**Figure 1 figure1:**
[figure not shown]
Veteran participant timeline. SUPPORT: Suicide Prevention by Peers Offering Recovery Tactics.

### Safety Procedures

#### Overview

At least one member of the on-call team of 3 licensed psychologists, who are part of the research team and employed at the VA San Diego Healthcare System, is available during all participant interactions. The on-call team is available for suicide risk assessments and appropriate triage as well as support to the research staff and peer specialists. The local suicide prevention coordinator team is also available on call during business hours for additional consultation.

#### Peer Specialist Participants

Peer specialist participants conduct a posttreatment assessment after completing SUPPORT with each veteran participant. To assess potential iatrogenic effects of delivering the intervention, peer specialist participants will complete the Negative Effects Questionnaire [26,27] (See peer specialist participant measure section below) as part of their posttreatment assessment. If the peer specialist participant reports that a negative effect occurred due to delivering the intervention and rate it as “very” or “extremely” impactful, research staff will notify the on-call psychologist to follow up with the peer specialist participant to determine whether additional support, such as referral to the employee assistance program, is needed. Described in more detail in the SUPPORT training section (subsection: Peer Specialist Training), peer specialists also receive ongoing support as part of the study supervision group and can request to meet individually with the principal investigator at any time.

#### Veteran Participants

Veteran participants referred to the study are gauged by a licensed VHA clinician as not needing immediate psychiatric hospitalization; however, as risk can change, veteran participants are assessed for suicide risk at multiple stages of the study. Peer specialists are trained in the SUPPORT safety protocol to directly screen for increasing veteran suicide risk at each SUPPORT appointment [18,28]. This protocol trains the peer specialists to contact the on-call psychologist during the appointment if suicide ideation is reported to be more severe since the last licensed VHA clinician’s assessment and if there is intent to act before the next meeting with a licensed VHA clinician. If suicide ideation is current but reported not to be more severe and it is not likely the veteran will act on their suicide thoughts, peer specialists are to review the veteran’s suicide safety plan and alert the on-call psychologist after the appointment concludes. A detailed procedure for this safety protocol is described in the work by Chalker et al [18].

All veteran participants will also be screened for suicide risk at screening, baseline, and all follow-up assessments by the research staff. Research staff are trained in an adapted version of the University of Washington Risk Assessment Protocol [29,30] to fit VHA protocols. Specifically, research staff are trained to alert the on-call psychologist while still with the participant if they report current active suicide ideation, a plan for suicide, access to lethal means, and intent to act on their plan in the following 48 hours—all of which are questions asked in the baseline and follow-up assessment batteries. If any of the previous criteria or any suicide behavior is reported during baseline and follow-up assessments, research staff are trained to alert the on-call psychologist to review the participant data, and the on-call psychologist will determine the appropriate next steps, for example, contacting the veteran for additional suicide risk assessment. Veterans are informed of limits to confidentiality such that, if they report increases in their acute suicide risk to research staff or peer specialists, their treatment team may be informed by the principal investigator to support continuity of care.

If a veteran participant is psychiatrically hospitalized at the local medical center, research staff and their assigned peer specialist as applicable will coordinate with the veteran’s broader treatment team to determine appropriate ongoing engagement. As part of their role, peer specialists can and do provide services in inpatient psychiatry settings.

### Peer Specialist Training

The SUPPORT training includes two 4-hour workshops tailored to the scope of a peer: SUPPORT 101 (a stand-alone general suicide prevention training) and the SUPPORT intervention training (a training for veteran peer specialists in how to provide the recovery-oriented, evidence-informed intervention for veterans with SMI at increased suicide risk). Training in the SUPPORT safety protocol is also provided. Chalker et al [18] provide a detailed description of the full training.

After the SUPPORT training, a study supervision group is held biweekly. This supervision is led by the principal investigator, who is a licensed clinical psychologist and trained as a peer specialist supervisor in the state of California [31]. Study supervision serves as a dedicated time to discuss immediate concerns; receive feedback on SUPPORT appointments; discuss and process general concerns, fears, and questions; receive support; and discuss implementation or other administrative topics. Peer specialist participants will continue to attend the regular supervision that they receive outside of the study that includes monthly group supervision with all local peer specialists and individual supervision with their direct clinical supervisor.

### SUPPORT Intervention Curriculum

#### Overview

The SUPPORT intervention was co-developed by veterans with lived experience and inspired by 4 evidence-based interventions: suicide safety planning [32,33], Whole Health [34], Wellness Recovery Action Plan [35], and compensatory cognitive training [36,37]. Therefore, the SUPPORT intervention integrates elements of value-based living, recovery and action planning, and compensatory cognitive strategies (called “learning strategies” in SUPPORT). The role of learning strategies is to enhance recall and engagement in plans for adaptive coping during high-risk situations, as well as to enhance recovery plans to work toward meaningful goals [38]. After learning strategies are introduced, the progress of using them is reviewed and updated as needed in subsequent appointments. The content is formatted into 4 modules (Table 1) that are delivered in weekly one-on-one via telehealth or in-person appointments for approximately 50 minutes, each in the usual clinic in which the peer specialists work. The peer specialist conducts brief check-in calls at 2 and 4 weeks after the final module to reinforce the intervention material and offer additional resources as needed. Following the SUPPORT safety protocol, if a veteran is screened to be at increased suicide risk and the on-call psychologist is required to join the appointment, the peer specialist and veteran may reschedule that module’s content to a separate appointment. A SUPPORT intervention note template is provided for peer specialists to document their encounters in the veteran’s electronic health record following their standard clinic procedures.

**Table 1 table1:** Peer-led Suicide Prevention by Peers Offering Recovery Tactics intervention curriculum.

Module number	Theme	Psychoeducation topics	Activities
1	Reasons for living	Recovery, values, and reasons for living	Identifying reasons for living by recognizing strengths and values
2	Hope	Wellness tools and hope kit	Developing wellness tools to feel well, stay well, and live the way they want to; developing a hope kit (a collection of reminders of one’s values, positive memories, and reasons for staying alive)
3	Recovery goal	Recovery goals, action steps, and goal planning	Creating a long-term recovery goal as well as short-, mid-, and longer-term action steps to work toward recovery goals, particularly when suicidal
4	Social connections	Social support and crisis support	Building and maintaining social support, how supports contribute to recovery and suicide prevention, identifying who to call in a suicide crisis, addressing barriers to contacting supports, and reinforcing alternative tools

A workbook is provided to all veterans, which they are encouraged to complete with their peer specialist as well as in between appointments. The prompts in the workbook encourage a conversation focused on recovery and suicide prevention, including building a SUPPORT plan. By the end of SUPPORT, veterans will have a completed SUPPORT plan with 4 reminders for living that map to each module. All SUPPORT appointments also have four objectives for the peer specialist to meet: (1) ask directly about suicide, (2) work on the SUPPORT plan, (3) build learning strategies, and (4) share relevant experiences.

#### Fidelity

All SUPPORT appointments are recorded, and adherence is coded using the SUPPORT fidelity measure—developed with input from both advisory boards who co-developed SUPPORT [18] and based on previous peer specialist fidelity work [39]. Adherence is evaluated at the appointment level. An adherent SUPPORT appointment is defined as meeting all 4 objectives. Given the pilot nature of the trial and development stage of the intervention, all recorded appointments will be coded for adherence by at least one coder to provide feedback to the peer specialist. Adherence ratings are shared weekly with peer specialists and discussed in the study supervision group; peer specialists can meet individually with fidelity coders or the principal investigator as needed. A total of 15% of all SUPPORT appointments will be randomly selected and rated by 2 coders to determine fidelity. If the 2 coders disagree about whether an appointment has reached adherence, a third coder will rate the appointment, and a consensus meeting will be held among the 3 coders.

### Enhanced Standard Care

SUPPORT will be compared to an enhanced standard of care delivered at the VA San Diego Healthcare System that contains the following elements: (1) suicide risk assessment, (2) VHA safety planning intervention, and (3) timely referral to VHA mental health outpatient care. Standard care is said to be enhanced as veterans randomized to this condition will also be assessed for suicide risk at baseline and follow-up assessments, which may result in additional clinical interactions.

### Data Collection and Management

#### Overview

To become an approved assessor, training includes live training by the principal investigator and online training as provided by certain measures such as the C-SSRS [40]. Assessors then sequentially conduct role-plays with approved assessors, shadow an approved assessor, and are finally observed and approved by a previously approved assessor. Data are collected by approved assessors and stored in a VHA-approved secure web application for building and managing online surveys and databases called REDCap (Research Electronic Data Capture; Vanderbilt University) [41,42]. REDCap has validity checks for individual variables (eg, whether the data are in the appropriate range) included in the project design. Once data are entered into REDCap, they are also checked by a separate research staff member. Laboratory meetings are held weekly to discuss data collection and management questions.

#### Feasibility and Acceptability Data

Feasibility is defined as attainment of recruitment goals (n=50 veterans; n=2 peer specialists) and a ≥70% retention rate for veterans at the end of the intervention. Acceptability for veterans is measured using the Client Satisfaction Questionnaire–8 [43]. While direct suicide prevention interventions have been only shown to be helpful [44,45] and our advisory boards did not anticipate any negative effects for veterans, we do ask 1 open-ended question after intervention completion or dropout to determine whether veterans found the intervention to be harmful. After each veteran participant completes or drops out of the intervention, the following acceptability item is asked of the peer specialist to rate on a 5-point Likert scale (1=not at all, 2=a little bit, 3=somewhat, 4=quite a bit, and 5=very much): “Overall, how satisfied are you with delivering the SUPPORT Intervention?” High satisfaction for peer specialists is defined as “quite a bit” or “very much” satisfied.

#### Peer Specialist Participant Measure

To track potentially negative effects for peer specialists, a revised and shortened version of the Negative Effects Questionnaire [26,27] is administered after each veteran participant completes or drops out of the intervention. The Negative Effects Questionnaire was revised from “receiving” to “delivering” an intervention and includes 8 yes or no items related to possible negative effects one might experience because of delivering the intervention. If any item is endorsed positively, two follow-up questions are asked: (1) “Indicate the severity of your experience (how negative the experience was for you)” (response scale: 0=not at all, 1=slightly, 2=moderately, 3=very, and 4=extremely) and (2) “Do you believe your experience was caused by the intervention you delivered or other circumstances that occurred during the same period as this intervention?” Traditional scoring may not be useful, so the Negative Effects Questionnaire results will be reported as (1) a total score of endorsed negative effects (range 0-8), (2) a total score of severity across all endorsed items (range 0-32), and (3) a total score of the negative effects being caused by the intervention (range 0-8).

#### Veteran Participant Measures

Veteran assessments are conducted at baseline and the 1-, 2-, and 3-month follow-ups. Table 2 shows the veteran participant measures. The measures included assess a range of standard outcomes important in the prevention of suicide, as well as including 2 laboratory-developed measures to explore SUPPORT’s potential unique impact on suicide prevention.

The primary outcome of personal recovery is measured using the 41-item Recovery Assessment Scale, a self-report measure of personal recovery with 5 domains: personal confidence and hope, willingness to ask for help, goal and success orientation, reliance on others, and no domination by symptoms [46]. The other primary outcome is assessed using interviewer -administered assessments of the 19-item Beck Scale for Suicide Ideation [47] for past-week suicide ideation severity and the C-SSRS [21,25] for past-month suicide ideation severity.

**Table 2 table2:** Veteran participant measures at all time points.

Timing and domain		Measure	Outcome type
**All time points**			
	Personal recovery	Recovery Assessment Scale–41	Primary
	Suicide ideation severity	Beck Scale for Suicide Ideation; C-SSRS^a^	Primary
	Psychosocial functioning	Specific Level of Functioning Scale	Secondary
	Quality of life	Brief version of the World Health Organization Quality of Life Scale	Secondary
	Cognitive strategy use	Cognitive Problems and Strategies Assessment	Exploratory
	Perceived burdensomeness and thwarted belongingness	Interpersonal Needs Questionnaire–15	Exploratory
	Hopelessness	Beck Hopelessness Scale	Exploratory
	Suicide behaviors	C-SSRS	Exploratory
	Suicide crisis service use	Chart review	Exploratory
**2-month follow-up only**			
	Peer impact	Laboratory-developed measure	Exploratory
**2- and 3-month follow-ups**			
	Suicide prevention strategy recall (SUPPORT^b^ plan and suicide safety plan)	Laboratory-developed measure	Secondary

^a^C-SSRS: Columbia–Suicide Severity Rating Scale.

^b^SUPPORT: Suicide Prevention by Peers Offering Recovery Tactics.

Secondary outcomes of psychosocial functioning and quality of life are measured using the Specific Level of Functioning Scale and the brief version of the World Health Organization Quality of Life Scale, respectively. The Specific Level of Functioning Scale is a 43-item self-report questionnaire assessing functioning on 4 domains (interpersonal, social acceptance, activities, and work) and has been determined to be the best measure of functioning for adults with schizophrenia to assess real-world functioning in 1 scale [48]. The brief version of the World Health Organization Quality of Life Scale is a 26-item self-report instrument assessing 4 domains of quality of life: physical health, psychological health, social relationships, and environment [49]. Collected only at the 2- and 3-month follow-up assessments, suicide prevention strategy recall (secondary outcome) is measured using laboratory-developed self-knowledge tasks in which veterans are given 10 minutes to say what they remember from each section of their SUPPORT plan (SUPPORT condition only) and suicide safety plan [50]. Each plan is scored based on standard safety planning scoring practices [51,52], with SUPPORT plan scores ranging from 0 to 4 and safety plan scores ranging from 0 to 18.

The exploratory outcomes are cognitive problems and strategy use, burdensomeness and belongingness, hopelessness, suicide behavior, service use, and peer impact. Cognitive strategy use is measured using 30 self-report items on memory and thinking strategies that have been successfully used with a population with SMI and designed to capture changes in the use of compensatory cognitive training skills [37], referred to as “learning strategies” in SUPPORT. Burdensomeness and belongingness, which, when they converge, according to the interpersonal theory of suicide [53], create suicide desire [54], are captured using a 15-item self-report measure. The Beck Hopelessness Scale is a 20-item true-or-false self-report measure that has been shown to be predictive of eventual suicide in psychiatric inpatients [55]. Suicide behavior is measured using the C-SSRS behavior section, and service use (ie, suicide-related emergency department visits and inpatient psychiatry stays, Veteran Crisis Line contacts, and outpatient visits) is captured via chart review. Finally, based on theories related to peer support [56-63] and the Peer Specialist Fidelity Measure–Veteran Version (previously used to establish fidelity in traditional VHA peer support programs [39]), we co-developed with our advisory boards a measure collected posttreatment to evaluate the peer impact of veterans receiving SUPPORT. This measure includes 17 Likert scale–rated items and 14 open-ended questions. Likert scale items are rated from 1 (not at all) to 5 (very much). These items will be summed to obtain a total score; a higher score indicates a higher impact of the peer specialist. Sample Likert scale items include the following: “How much did your peer specialist encourage you to be hopeful?” and “How much did you feel connected with your peer specialist?” Open-ended items are asked to better understand the Likert scale–rated items (eg, “What did you have in common with your peer specialist that helped you connect?”).

### Veteran Participant Sample Size Determination

The sample size for the pilot randomized controlled trial was estimated using a previous method provided by Hedeker et al [64] and the Repeated Measures and Sample Size software. This minimum power estimation is based on a 5% attrition rate per time point, correlation of 0.5% of repeated measures, and medium to large effect sizes. A total sample size of 44 will yield a minimum of 80% power to detect a large effect size, defined as a between-group difference increasing linearly from 0 at baseline to 0.7 SD units at the last time point. A large effect size was chosen as this is a pilot feasibility study and is not intended to be powered to detect a small or medium effect [65].

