**Methods:**

A pilot randomized controlled trial with 50 veterans randomized into 2 groups will be conducted. Participants will be recruited from the Veterans Affairs San Diego Healthcare System. Veterans with SMI and past-1-month active suicide thoughts or past-3-month suicide behavior as defined by the Columbia–Suicide Severity Rating Scale will be included. Enrolled veterans will be randomized to receive SUPPORT or enhanced standard care. All veteran participants will be assessed at baseline and the 1-, 2-, and 3-month follow-up assessments. Feasibility is defined as attainment of recruitment goals and a ≥70% retention rate. Acceptability for veterans is measured using the Client Satisfaction Questionnaire–8. Acceptability for peer specialists is measured using a satisfaction question rated on a 5-point Likert scale. Primary outcomes are measured using the Recovery Assessment Scale–41 (personal recovery), as well as the Beck Scale for Suicide Ideation and the Columbia–Suicide Severity Rating Scale (suicide ideation severity). Secondary outcomes are measured using the Specific Level of Functioning Scale (functioning), the brief version of the World Health Organization Quality of Life Scale (quality of life), and a laboratory-developed self-knowledge task (suicide prevention strategy recall). Outcomes will be tested using mixed-effects models. Safety procedures for all participants are discussed.

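### The stated minimum of 80% power at a total of 44 is not reproduced by a two-sided 5% linear trend test on the printed inputs: about 64–65% at 44 and 70–71% at the 50 to be randomised

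*Protocol article*

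**What the plan says.** The section Veteran Participant Sample Size Determination states that "A total sample size of 44 will yield a minimum of 80% power to detect a large effect size", and specifies that effect as "defined as a between-group difference increasing linearly from 0 at baseline to 0.7 SD units at the last time point". The calculation is "based on a 5% attrition rate per time point" and on a "correlation of 0.5% of repeated measures, and medium to large effect sizes". It cites a published repeated-measures method "and the Repeated Measures and Sample Size software". It gives no alpha, sidedness, covariance shape or test contrast.

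The number of visits comes from Veteran Participant Measures: "Veteran assessments are conducted at baseline and the 1-, 2-, and 3-month follow-ups". The number to be randomised comes from the Methods part of the abstract: "A pilot randomized controlled trial with 50 veterans randomized into 2 groups will be conducted".

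Under Primary and Secondary Outcomes, inference is assigned to a mixed model that is fully saturated in treatment and visit, so it is not a linear trend model. The Overview of Analysis of Outcomes makes feasibility and acceptability the primary goal and concedes that the outcome analyses may lack power. Limitations and Future Directions repeats that concession.

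**The concern.** With four visits, an effect shape, a correlation and an attrition rate all printed, power is fixed once alpha, sidedness, allocation and covariance shape are assumed. Under the conventional choices the result is about 15 percentage points below the printed figure, which the article presents as a minimum.

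Aim 2 uses preliminary impact to judge whether a larger trial is warranted. A reader who accepts 80% takes a true 0.7 SD effect to be missed about 1 time in 5. On the trend test it would be missed about 36% of the time at 44 (100 − 64) and 30% at 50 (100 − 70). A null result would then look like stronger evidence against SUPPORT than it is.

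**Working it through.** **Inputs from the article.** Total 44 (planned 50); visits at months 0, 1, 2, 3; difference 0, 0.233, 0.467, 0.7 SD; 5% loss per time point, so 100%, 95%, 90.25% and 85.7% observed; correlation 0.5.

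**Assumptions, not in the article.** Two-sided 5% test, 1:1 allocation, compound symmetry, "correlation of 0.5% of repeated measures" read as 0.5, normal approximation.

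**Hand check without attrition, total 44.**
- Slope variance per participant = (1 − 0.5)/Σ(t − t̄)² = 0.5/5 = 0.1
- Slope difference = 0.7/3 = 0.2333
- SE = √(2 × 0.1/22) = 0.0953
- z = 0.2333/0.0953 = 2.447
- Power = Φ(2.447 − 1.960) = 68.7%

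Attrition can only lower this, so 80% is already out of reach for this test.

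**With the stated attrition, contrast formula.** Per-arm numbers at 44 are 22, 20.9, 19.86 and 18.86. The contrast is c = (−1.5, −0.5, 0.5, 1.5).
- Effect = Σ c·δ = 0 − 0.117 + 0.233 + 1.05 = 1.167
- SE = √(2 ΣΣ c_s c_t ρ_st/√(n_s n_t)), with ρ_st = 1 when s = t and 0.5 otherwise: 0.497 at 44 and 0.466 at 50
- z = 2.348 at 44 and 2.503 at 50
- Power = 65.1% at 44 and 70.6% at 50

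**Same inputs, generalised least squares slope with monotone dropout.** SE of the slope difference is 0.1006 at 44 and 0.0944 at 50, so z = 2.318 and 2.471, and power is 64.0% and 69.6%. A simulation of 4,000 trials gave 63.7% and 69.9%.

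**Sample size and detectable effect.** 80% power needs a total of 64 (contrast formula) or 66 (least squares). The effect detectable with 80% power is 3 × SE × (1.960 + 0.842): about 0.85 SD at 44 and 0.79 SD at 50.

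**Attempts to recover 80% at a total of 44.**

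| Variant | Power |
|---|---|
| One-sided 5% trend test, stated attrition | 75–76% |
| One-sided 5% trend test, attrition ignored | 78.9% |
| Two-sided trend test, baseline means constrained equal, stated attrition | 76.4% |
| Correlation taken literally as 0.005, two-sided | 38.5% |
| Baseline-constrained trend and one-sided test | 84.9% |
| Baseline-constrained saturated model, 3-month contrast, one-sided | 80.4% |
| Baseline-constrained trend, two-sided, attrition ignored | 81.4% |
| Correlation about 0.65 instead of 0.5, two-sided contrast formula | 80.0% |
| Constant 0.7 SD at all four visits, average over visits, two-sided, stated attrition | 80.6% |

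The first four rows fall short. The next two combine two choices that the article does not state. The last three each change a stated input: attrition, correlation or effect shape.

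**The model named for inference.** For the saturated treatment-by-visit model with unconstrained baseline, the 3-month change has SE 0.318 at 44 and 0.298 at 50, so z = 2.201 and 2.346. Power is 59.5% and 65.0%.

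**The case against.** The strongest reply is that 64% is conditional. The article states no alpha, sidedness, covariance shape or contrast, and an article may leave these to the full protocol or SAP. Its hypotheses are directional and the effect is set to 0 at baseline, so a one-sided test with baseline means constrained equal is conceivable. That pair does reach 80–85% at 44 with every printed input kept. This part stands: the printed inputs alone do not make 80% impossible, so the point must carry its assumptions. It does not validate the figure, because the article states neither choice and either one alone falls short at 44. At 50, a one-sided trend test (about 80%) or a two-sided baseline-constrained trend test (81%) would get there, but the claim is made for 44.

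The second reply is that the article already discounts its power, in the Overview of Analysis of Outcomes and in the limitations, and that feasibility comes first. No go/no-go rule tied to significance is stated. This limits the consequence. It does not withdraw the 80%, so the article now contains both the caveat and the unqualified minimum.

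A reader might also infer where 44 came from. An effect of 0.8 SD without attrition gives 79.9%, and a constant 0.7 SD effect with the stated attrition gives 80.6%, with 44 the smallest even total that reaches 80%. The two explanations are incompatible and the article supports neither, so no origin should be asserted.

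**Conclusion.** The 80% figure at 44 is not reproduced under a two-sided 5% linear trend test with 1:1 allocation, compound symmetry and correlation 0.5. Power is about 64–65% at 44 and 70–71% at 50. Among the variants tried, 80% at 44 appears only when a one-sided test is combined with a baseline constraint, or when a stated input is changed.

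A reader might conclude that the trial is too small and should enrol more. The article does not support that: it is a pilot with feasibility as its primary goal, and it disclaims power for small or medium effects. The consequence is moderate and confined to how an Aim 2 null result is read.

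**What to change.** Reconcile the paragraph with the inputs actually entered in the software, and restate the power with its test and at the number to be randomised. Suggested wording: *With 50 randomised 1:1, two-sided alpha 0.05, correlation 0.5 and 5% loss per follow-up, power for a 0.7 SD difference at 3 months is about 70% for the linear trend test and about 65% for the 3-month change contrast of the saturated model; 80% power for the trend test corresponds to about 0.8 SD.*

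If the software run used a different effect shape, describe that shape instead. Change the correlation from 0.5% to 0.5.

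The cost is rewording one paragraph and reporting a less favourable figure. Enrolment, conduct and analysis do not change.
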